### Sample size estimation

We will evaluate 5 candidate predictors for the R model, 7 for the T model, and 3 for the HA model as specified in Fig. 1. Following the recommendation of having at least 10 events per predictive variable and assuming that:

Approximately 50% of women with eoPE deliver within ≤ 7 days [14], the required sample size to validate the T model is: 7 (predictive features) x 10 (events) / 0,5 (event incidence) = 140 eoPE casesApproximately 40% of women with eoPE experience any PE-related complication, and in 20% these complications include placental abruption or HELLP syndrome [30]. According to this, the required sample size to validate the R model is: 5 (predictive features) x 10 (events) / 0,4 (event incidence) = 125 eoPE cases, and to validate the HA model is: 3 (predictive features) x 10 (events) / 0,2 (event incidence) = 150 eoPE cases

This estimation assumes independence among predictor variables. However, ML techniques can identify dependencies between variables when present, which could potentially reduce the required sample size. Nonetheless, we have chosen to maintain the estimate of 200 cases, as it is the most conservative assumption and aligns with the sample size used in our previous work during model development, providing greater confidence.

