### Models’ validation strategy

An analysis will be conducted after the inclusion of the first 100 participants to perform an initial external validation of the predictive models. This validation will include both quantitative and semi-quantitative assessments:

The quantitative evaluation will focus on the diagnostic performance of the predicted risks, including the estimation of sensitivity, specificity, positive and negative predictive values, discrimination using the area under the ROC curve, calibration using the Hosmer–Lemeshow test, and clinical utility assessed through decision curve analysis.The semi-quantitative evaluation will consider clinicians’ perceptions of the information provided by the models. After reviewing the model’s information, they will be asked to answer four questions to assess the perceived usefulness and potential clinical impact of the predictions: (1) overall appreciation of the information (“I like it / I don’t like it”); (2) whether this information would have influenced their decision regarding corticosteroid administration (“No / Yes, I would have administered them earlier / Yes, I would have administered them later”); (3) whether it would have modified their management of hospitalization between diagnosis and delivery (“No / Yes, I would have extend the duration of hospitalization / Yes, I would have reduced it”); and (4) whether it would have changed their decision about the timing of delivery (“No / Yes, I would have indicated delivery earlier / Yes, I would have delayed delivery”).

Following this first phase, the ML training methodology will be replicated incorporating the information from the initial 100 cases, and the updated models will then be applied prospectively to the next 100 participants. This “re-training” methodology begins with a preprocessing stage, which includes missing-value imputation using MissForest, outlier removal, standardization of numerical variables with Standard Scaler, and encoding of categorical variables using OneHot and Label encoding [34]. Subsequently, model training is carried out using genetic algorithms within a multi-objective framework. These algorithms are non-deterministic, can be adaptive, and often benefit from parallel computation, enabling them to search for high-quality approximate solutions [35].

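### The protocol says validation needs 140, 125 and 150 women, yet the initial validation and the test of the retrained models have 100 each, and events per variable does not size the validation of a fixed model

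*Protocol article*

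**What the plan says.** Sample size estimation fixes the predictor counts ("We will evaluate 5 candidate predictors for the R model, 7 for the T model, and 3 for the HA model") and sizes the study by a rule: "Following the recommendation of having at least 10 events per predictive variable". It assumes for T that "Approximately 50% of women with eoPE deliver within ≤ 7 days", and takes incidences of 40% for R and 20% for HA. The R and HA results are given as "5 (predictive features) x 10 (events) / 0,4 (event incidence) = 125 eoPE cases" and "3 (predictive features) x 10 (events) / 0,2 (event incidence) = 150 eoPE cases"; the T result is 140. Each is described as the number required to validate that model. The section then says "we have chosen to maintain the estimate of 200 cases, as it is the most conservative assumption", adding that 200 is in line with the size used in development.

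Models' validation strategy divides those women. For the original models: "An analysis will be conducted after the inclusion of the first 100 participants to perform an initial external validation". Those 100 then enter retraining, and "the updated models will then be applied prospectively to the next 100 participants". A final validation follows once 200 women are recruited, comparing original and retrained models with a paired DeLong test. The women it analyses are not named.

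Table 1 and the Workflow section show that the application runs T and HA only when the R prediction exceeds 0.5.

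**The concern.** External validation is the primary objective. A reader of the sample-size section would conclude that 200 women comfortably exceed what each model needs. The two validation steps with a stated size have half that number and miss the plan's own requirement for every model.

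The rule is also aimed at a different task. Events per variable limits overfitting while a model is being fitted. A fixed model has nothing fitted at validation. Its precision depends on the numbers of women with and without the event, not on how many predictors the model holds. A study can therefore meet the rule and still give intervals too wide to show whether performance has carried over from development.

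**Working it through.** **Inputs.** Predictors: T 7, R 5, HA 3. Incidences: T 0.5, R 0.4, HA 0.2. Rule: 10 events per predictor. All are from Sample size estimation. Development sensitivity of the simplified models (Background): R 60%, T 68%, HA 92%; R specificity 74%. No AUC is given, so I assume 0.70 to 0.80.

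**1. The plan's own figures.** N = predictors × 10 / incidence.
- T: 7 × 10 / 0.5 = 140
- R: 5 × 10 / 0.4 = 125
- HA: 3 × 10 / 0.2 = 150

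All three reproduce. The largest is 150, so 200 exceeds each of them but is not the result of any.

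**2. The same rule applied to 100 women.** Events = 100 × incidence; events per variable = events / predictors.

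| Model | Events expected | Events the rule needs | Events per variable | Shortfall in women |
|---|---|---|---|---|
| T | 50 | 70 | 50/7 = 7.1 | 140 − 100 = 40 |
| R | 40 | 50 | 40/5 = 8.0 | 125 − 100 = 25 |
| HA | 20 | 30 | 20/3 = 6.7 | 150 − 100 = 50 |

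For the retrained models this assumes that the feature counts stay at 7, 5 and 3.

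**3. Which women the final comparison can use.** A paired DeLong test needs both models scored on the same women. The retrained models have learned from the first 100, so only the second 100 are out of sample for both. The unchanged original models have learned from none of the 200 and could be scored on all of them. The document does not say that they will be.

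**4. Why the rule does not fit.** Background describes a 25-variable R model. The rule would ask 25 × 10 / 0.4 = 625 women to validate it, against 125 for the 5-variable version. At the same n, event rate and observed sensitivity, the interval for sensitivity would be identical. This only illustrates the rule; the plan does not size the 25-variable model.

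**5. Precision.** Wilson 95% intervals for sensitivity at, or for HA close to, the development values:

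| Model | 100 women | 200 women |
|---|---|---|
| T | 34/50: 54–79% | 68/100: 58–76% |
| R | 24/40: 45–74% | 48/80: 49–70% |
| HA | 18/20: 70–97% | 36/40: 77–96% |

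HA is held at 90% in both columns, because 92% of 20 is not a whole number of women.

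AUC 95% half-width = 1.96 × SE, with the Hanley–McNeil SE = √{[A(1−A) + (n₁−1)(Q₁−A²) + (n₀−1)(Q₂−A²)] / (n₁n₀)}, Q₁ = A/(2−A), Q₂ = 2A²/(1+A), n₁ events and n₀ non-events. Example, R at A = 0.70 with 40 events and 60 non-events: SE = 0.055, half-width 0.107. Ranges for A from 0.70 to 0.80:

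| Model | 100 women | 200 women |
|---|---|---|
| T | 0.102–0.087 | 0.072–0.061 |
| R | 0.107–0.093 | 0.076–0.066 |
| HA | 0.138–0.123 | 0.098–0.087 |

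**6. The R > 0.5 gate.** At the development figures, the share above 0.5 is 0.4 × 0.60 + 0.6 × (1 − 0.74) = 0.24 + 0.156 = 0.396. That is about 40 of 100 women, or 79 of 200. If T and HA were analysed only in those women, even 200 recruits would leave fewer than the 140 and 150 stated. If R picks up HELLP or abruption cases at its overall 60% sensitivity (an assumption), 100 women would give 20 × 0.60 = 12 HA events.

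**The case against.** The best defence is that the study does recruit 200 women, more than the largest stated requirement, and that a final validation follows. A reader might infer from the split that every validation in the plan rests on 100 women. The text does not support that: the final set is unnamed, and the original models could be scored on all 200. What stands is that the two steps with a stated size have 100 each, and that an out-of-sample test of the retrained models cannot have more.

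A reader might also take the first analysis to be presented as confirmatory. It is not; the plan calls it initial.

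Nor was the sample reduced on the strength of machine learning. The remark that dependencies between variables might lower the requirement is followed by the decision to keep 200. It has no term in the calculation and supports nothing, but it does no numerical harm. Likewise, the plan does not claim that 200 comes out of one of the three formulas; it also appeals to the development sample (234 women in Background). That appeal says nothing about validation precision.

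The roughly 25 to 30 point widths apply to sensitivity. At 100 women, specificity at the development values is somewhat tighter, at about 19 to 22 points.

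**Conclusion.** The concern holds as a mismatch between the stated justification and the described design. It is not an arithmetic error, since all three calculations are correct. The initial validation and the evaluation of the retrained models each fall 40 (T), 25 (R) and 50 (HA) women short of what the protocol says is required, with 6.7 to 8.0 events per variable against its 10. The set for the final validation is unspecified.

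Separately, the rule is the wrong basis for sizing the validation of a fixed model, so meeting it would not show adequate precision.

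The event counts rest on the plan's incidences. The sensitivity intervals rest on performance at or near the development values, the AUC half-widths on an assumed 0.70 to 0.80, and the gated counts on development sensitivity and specificity for R. Whether T and HA will be analysed only above the gate is not stated, so that further loss is conditional.

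**What to change.** Restate Sample size estimation and Models' validation strategy so that they agree:

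1. Name as the primary external validation the unchanged original models scored on all 200 women. Compute T and HA for every woman in the analysis, whatever the R prediction. The Abstract says all model variables are recorded, so this can be done offline and the application's workflow need not change. Without it, 200 recruits would not secure the stated 140 and 150 for T and HA.
2. State that the retrained models, and the paired DeLong comparison, are evaluated only on the second 100 women, with about 50 (T), 40 (R) and 20 (HA) events, and that this is below the plan's own 140, 125 and 150.
3. Replace the events-per-variable argument, and the sentence that machine learning could reduce the size, with expected 95% interval widths for sensitivity, specificity and AUC at 100 and 200 women. Show the assumed AUCs as a range.

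The cost is some extra offline scoring, revised text and a less favourable statement of adequacy. No additional patients are needed.

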### Study variables

#### Dependent variables

Below are the outcomes assessed in each model:R Model: presence of at least one of the following adverse maternal events (yes/no):◦ Pulmonary edema confirmed radiologically and associated with oxygen saturation <95%.◦ Acute kidney injury (creatinine ≥1.6 mg/dL or an increase ≥1.0 mg/dL from baseline) or oliguria (<500 mL/24 h).◦ Refractory hypertension: severe and uncontrolled elevation of blood pressure for >12 hours despite the use of at least three antihypertensive medications.◦ Neurological events: hemorrhagic stroke, coma (Glasgow Coma Scale <13), posterior reversible encephalopathy syndrome, or cortical visual loss including retinal detachment.◦ HELLP syndrome: hemolysis (bilirubin ≥1.2 mg/dL, LDH ≥600 IU, or diagnosis by peripheral smear), elevated transaminases (AST ≥70 IU/L), and platelet count <100,000/mm³. Cases meeting two of the three criteria (incomplete HELLP) will also be included.◦ Placental abruption: partial or complete separation of the placenta from its normal uterine implantation site before completion of the second stage of labor. Diagnosis requires evidence of an organized retroplacental hematoma involving at least 20% of the implantation area.T model: interval between the diagnosis of eoPE and delivery ≤7 days (yes/no)HA model: presence of HELLP syndrome or abruptio placentae (yes/no)

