### Inclusion criteria

Eligible patients are pregnant women meeting all of the following criteria: (1) maternal age ≥ 18 years; (2) singleton pregnancy; (3) diagnosis of PE established according to the criteria of the International Society for the Study of Hypertension in Pregnancy [11]; (4) gestational age at the time of diagnosis between 20 + 0 and 33 + 6 weeks; (5) availability of angiogenic biomarker results (sFlt-1/PlGF ratio) obtained at the time of diagnosis (± 3 days); and (6) provision of written informed consent to participate in the study.

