#### Independent variables

The models draw on maternal demographic information and clinical data obtained at the time of eoPE diagnosis, including laboratory parameters, angiogenic biomarkers (sFlt-1/PlGF), and ultrasound findings. Below, the predictor variables used in each specific model are described in detail:

R model features: pulsatility index in the middle cerebral artery < percentile 5, gestational age at PE onset, number of antihypertensive administrated drugs, pulsatility index of the right uterine artery, previous PET model features: PlGF < percentile 5, sFlt-1/PlGF clinical classification, weight, personalized percentile of estimated fetal weight, pulsatility index of the left uterine artery, chronic hypertension and multiples of the median of the mean pulsatility index of the uterine arteriesHA model features: sFLt1 > percentile 95, PlGF clinical classification, PlGF < percentile 5

The models do not incorporate information related to the care center or socioeconomic status. They also do not include data on perinatal care; however, the study does collect the main perinatal outcomes for descriptive purposes. The complete set of variables collected for this study is detailed in Additional file 1.

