### Data collection

Data collection constitutes a critical phase of the study, as the quality and completeness of the information recorded will directly determine the robustness and validity of the subsequent external validation analyses. Study data are entered and managed is performed through a dedicated database developed for this purpose on the REDCapTM platform. It allows participating centers to create and complete electronic case report forms in real time and supports data import and export in multiple formats, including Microsoft Excel, PDF, SAS, Stata, R, and SPSS.

The designated clinician at each participating center will be responsible for recording all patient data in REDCap™, covering the period from the start of pregnancy until delivery. Each participant will be assigned a unique identification code that decouples clinical data from personally identifiable information. The linking file containing the correspondence between study codes and personal identifiers will be stored securely and accessible only to a limited number of authorized persons. Thus, the data complies with the Personal Data Protection and Guarantee of Digital Rights and Regulation (EU) 2016/679 of the European Parliament and of the Council of April 27, 2016 on Data Protection (GDPR).

In this sense, the first and last sections of the database are particularly important and are described in detail in Additional file 1. In the first section (“Patient ID”), the clinician must enter the patient’s medical record number (MRN), which is immediately encrypted to ensure full anonymization. The clinician must also confirm that the inclusion and exclusion criteria are met and record the date on which informed consent was signed.

In the final section (“Semi-quantitative assessment”), a link to the web application is provided. The appearance of the application interface is shown in Additional file 2. Once the data used by the models and the delivery information have been entered into the database, the clinician can access the application to obtain the model outputs and complete the semi-quantitative assessment. Both the model outputs and the clinicians’ responses will be automatically stored in this section under the corresponding patient’s record. This retrospective appraisal minimizes optimism bias and allows the evaluation to reflect the clinical value of the predictions rather than responses influenced by the models themselves.

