### Workflow

Upon accessing the application, the user enters the patient’s MRN on the welcome page. This identifier is encrypted using a one-way hash function before any query is made. The application connects to the REDCap™ database to check whether the encrypted medical record number exists.

If the encrypted medical record number exists, the corresponding record ID is retrieved and the associated data are automatically loaded into the input forms.If it does not exist, a new REDCap™ record is created with the encrypted identifier, and the forms are displayed empty for manual data entry.

After entering the clinical, analytical, and ultrasound variables, the R model provides the predicted probability of maternal complications.

If the predicted risk exceeds 0.5, the forms for the HA and T submodels are automatically displayed. Once these variables are entered, both predictions are generated, and the clinician proceeds to complete the survey. The model outputs together with the survey responses are then sent to REDCap™.If the predicted risk is lower than 0.5, the clinician is redirected directly to the survey, and the probability estimated by the R model along with the survey responses is stored in REDCap™.

Finally, the application allows the user to reset the session and initiate the workflow for a new patient.

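### The R and HA outcomes have no time origin and recording ends at delivery, so the reported accuracy can mix detection of existing complications with prediction and can miss postpartum events

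*Protocol article*

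**What the plan says.** All references are to the protocol article.

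- **Outcomes (Dependent variables).** R is "presence of at least one of the following adverse maternal events (yes/no". The other acute-event outcome reads "HA model: presence of HELLP syndrome or abruptio placentae (yes/no". Neither has a start or an end date. T, in the same list, has both: "interval between the diagnosis of eoPE and delivery ≤7 days (yes/no".
- **Who is in.** The inclusion and exclusion criteria do not remove a woman who already has one of the listed complications. The Background accepts end-organ dysfunction as one route to the diagnosis of preeclampsia, and the R definition counts incomplete HELLP (two of three criteria) as an event.
- **When inputs are taken.** Independent variables places them at diagnosis. Inclusion criterion 5 requires "availability of angiogenic biomarker results (sFlt-1/PlGF ratio) obtained at the time of diagnosis", with a tolerance of 3 days either side.
- **When recording stops.** Data collection describes it as "covering the period from the start of pregnancy until delivery". Dates of the study and Study regimen also end at delivery.
- **Aim.** The Background and the Objectives speak of complications that develop, that is, incident events.

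**The concern.** The aim is prediction from the time of diagnosis, but the label does not separate what comes after that time from what was already there. A laboratory finding that establishes the diagnosis can also be scored as the predicted outcome. For HA, a HELLP event on day 1 can precede a day 3 sample that is then said to predict it.

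At the other end, five of the six R components (all but abruption), and the HELLP half of HA, can begin after birth. If the record closes at delivery, those women can be coded as event-free.

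These labels feed every accuracy, calibration and decision-curve result in Models' validation strategy. The first 100 cases are then used for retraining, so any mislabelling passes into the updated models. The Background also faults an existing model for relying on indicators of established organ dysfunction. Without a time origin, this study cannot show that its own models do something different.

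**Working it through.** **1. The plan's own figures.** Sample size estimation uses N = predictors × 10 / event incidence.

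- T: 7 × 10 / 0.5 = 140
- R: 5 × 10 / 0.4 = 125
- HA: 3 × 10 / 0.2 = 150

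All three reproduce. At 40% and 20%, 200 women give 80 R events and 40 HA events.

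**2. Events already present at the index time.** Let f be the share of events already present (assumed; the documents give none). If those women leave the at-risk set, enrolled N = predictors × 10 / [p(1 − f)] and events in 200 women = 200 × p × (1 − f).

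| f | R: N | R: events in 200 | HA: N | HA: events in 200 |
|---|---|---|---|---|
| 0 | 125 | 80 | 150 | 40 |
| 10% | 139 | 72 | 167 | 36 |
| 20% | 157 | 64 | 188 | 32 |
| 30% | 179 | 56 | 215 | 28 |

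By the plan's own rule, HA needs the full 200 at f = 25%: 30 / (0.2 × 0.75) = 200.

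**3. Effect of those events on sensitivity.** Apparent sensitivity = Se(1 − f) + s·f, where s is the rate at which already-present events are flagged (assumed). Take the Background's 60% for simplified R as the sensitivity for incident events, which is also an assumption.

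- s = 60%: no change.
- s = 80–95%: 62–63.5% at f = 10%, and 66–70.5% at f = 30%.
- s = 40%: 0.60 × 0.70 + 0.40 × 0.30 = 54% at f = 30%.

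The sign depends on s, which the documents do not give. For HA (sensitivity 92%), even s = 100% gives only 0.92 × 0.90 + 0.10 = 92.8% at f = 10% and 0.92 × 0.75 + 0.25 = 94% at f = 25%.

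**4. Postpartum events coded as non-events.** Let g be their share of all events (assumed), flagged at the same rate as other events.

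- Apparent specificity = [(1 − p)Sp + pg(1 − Se)] / [(1 − p) + pg]
- Apparent PPV = p(1 − g)Se / [pSe + (1 − p)(1 − Sp)]

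Inputs from the Background: R 60%/74% and HA 92%/52% (sensitivity/specificity).

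| g | R specificity | R PPV | HA specificity | HA PPV |
|---|---|---|---|---|
| 0 | 74% | 60.6% | 52% | 32.4% |
| 10% | 71.9% | 54.5% | 50.9% | 29.2% |
| 20% | 70.0% | 48.5% | 49.9% | 25.9% |
| 30% | 68.3% | 42.4% | 48.9% | 22.7% |

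Negative predictive value moves the other way, because unflagged postpartum events become true negatives. For R it goes from 0.444 / 0.604 = 73.5% to (0.444 + 0.016) / 0.604 = 76.2% at g = 10% and (0.444 + 0.048) / 0.604 = 81.5% at g = 30%.

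**5. Limits on g.** Abruption is defined as "separation of the placenta from its normal uterine implantation site before completion of the second stage of labor", so it cannot be postpartum. The Background gives HELLP in 12% and abruption in 11% of expectantly managed women. If that mix applied here without overlap, g = 30% for HA would need 0.30 × 23 / 12 = 57.5% of HELLP cases to be postpartum, so the upper HA rows are extreme. The HA rows also treat the model as run in all women, whereas the application runs it only when R exceeds 0.5.

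**The case against.** The strongest reply is that the intent is clear and the detail may sit elsewhere. The article speaks of developing complications and of incidence, fixes inputs at diagnosis, and refers to Additional file 1 (not shown) for the full variable list, where onset dates may be recorded. It also collects perinatal outcomes, so closure at delivery may not be literal. This stands in part: no sentence says that existing events are scored as predicted or postpartum ones as absent. But dates in a form do not supply a rule for using them, and three sections give delivery as the end. The two-month extension in Dates of the study is calendar time for the last women enrolled; no postpartum window per woman is stated.

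A reader might go further in four ways that the documents do not support:

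- **Sensitivity is inflated from 60% to 64–70%.** That needs every already-present event to be flagged (0.60 × 0.90 + 0.10 = 0.64; 0.60 × 0.75 + 0.25 = 0.70). No simplified R or HA input is an organ-function test, so full flagging has no basis.
- **Some 4–12 of 40 R events per 100 women are lost postpartum.** This applies 10–30% to all R events, including abruption.
- **R's input and outcome overlap by construction**, because "number of antihypertensive administrated drugs" is an input and refractory hypertension on at least three drugs is an outcome component. A count taken at diagnosis is a legitimate predictor of later refractory hypertension; it only needs a fixed date.
- **Inputs are entered with the outcome known**, because for an unknown record number "the forms are displayed empty for manual data entry". Data collection requires model data and delivery information in the database before access. The two passages do not fit together, but that is a workflow matter and not part of this point.

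An index time later than diagnosis also drops some true early events, although the Discussion places use at diagnosis. That is a fair cost, but a score cannot exist before its inputs do.

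**Conclusion.** The point holds as a defect in the outcome definition and recording window. Followed as written, the plan can count existing complications as R or HA events, lets an HA event precede its inputs, and can code postpartum events other than abruption as absent. The accuracy reported would mix detection with prediction.

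Its size and net direction are unknown. The figures above rest on assumed values of f, g and s, and the effects differ in sign across metrics. The biomarker window matters for HA and for T, not for simplified R, which has no angiogenic input. For T, a day 3 sample leaves 7 − 3 = 4 days of the horizon, which is the extreme case. The stated sample sizes are arithmetically correct; what changes is how many events count towards them.

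**What to change.** - Define the index time for each model as the later of diagnosis and that model's last input. Take the antihypertensive count as of that time.
- In the main R and HA analyses, include only women free of that model's outcome at the index time, and count events with onset after it. Women with an earlier event leave the denominator and are not recoded as non-events.
- Tabulate women with earlier events separately, and report the all-events analysis alongside for comparability with the development cohort.
- Keep event recording open from delivery to hospital discharge, and align Dates of the study, Study regimen and Data collection with this.
- Restate the expected event counts in Sample size estimation.

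The cost is extracting onset and input dates from existing charts, keeping records open to discharge, and having somewhat fewer events in the main analysis. HA has the least room: its 200 women suffice under the plan's own rule only while no more than 25% of events are already present. Recruitment is described as ongoing, so the rule can still be set before the final analysis.
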